### Statistical analysis

2.11

All statistical analyses will be performed using SAS version 9.2 (SAS institute Inc., USA). The total score of K-WOMAC and the change of score of each item will be analyzed using paired *t* test, and the degree of change between test and the control group at each time point will be determined according to normality satisfaction. A *t* test or Wilcoxon rank sum test will be performed to evaluate whether there is a statistically significant difference. In addition, a generalized linear model (GLM) will be performed with the following variables (age, gender, obesity). The total scores of VAS, SF-36, ESR, and CRP and the change of scores of each item will be analyzed by paired *t* test, and the degree of change between the test group and the control group at each time point will be normalized. Two sample *t* test or Wilcoxon rank sum test will be used to evaluate whether there is a statistically significant difference. In addition, the GLM will be implemented with the following variables (age, gender, obesity) as the covariate, and if there is a statistically significant difference among the baseline characteristics, the GLM will be considered as the covariate. All treatment-emergent adverse events (TEAEs) that occur after ingestion of human trial foods will be coded according to MedDRA, and all adverse events that will occur after ingestion of human trial foods will be tabulated and evaluated for incidence. The proportion of human subjects with adverse reactions between groups will be calculated and analyzed using Chi-square test or Fisher exact test.

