#### Primary outcomes

2.8.1

Korean-Western Ontario and McMaster Universities (K-WOMAC) index. The K-WOMAC index will measure changes in joint pain at the end of week 6 and 12 to compare those with the baseline scores.

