### Sample size

2.10

The sample size will be calculated following a previously described method where the VAS score in the test group decreased from ∼4.2 to ∼25.4, whereas the VAS score in the placebo group increased from ∼40.9 to ∼41.^[6]^ We also assume that the change in the VAS score in our test and placebo groups will be −16.6 and +0.1, respectively. The following parameters will be considered to determine the size of the sample:

Superiority test

Level of significance, a = 0.05 Two-sided test

b = 0.2, power of test = 80%

Ratio of the number of subjects in the test and placebo groups, l = 1, n_t_ (subject number of the test group) = ln_c_ (subject number of the placebo group)

Difference between the groups, D = 16.7

Standard deviation, s = 27.04 (in both groups)

We assume that with a dropout rate of 25%, 37 participants will be included in each group.

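### The K-WOMAC comparison tests unadjusted change, and its GLM omits the baseline score; adding that covariate is a free gain in precision of uncertain size

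*Protocol article*

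**What the plan says.** The primary outcome is K-WOMAC, measured at weeks 6 and 12 "to compare those with the baseline scores" (Primary outcomes). The Study design section schedules a baseline assessment at week 0.

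The Statistical analysis section uses a paired t test within groups. It then compares the change between groups at each time point with a t test or Wilcoxon rank sum test, depending on normality. Neither test takes a covariate. The section continues: "In addition, a generalized linear model (GLM) will be performed with the following variables (age, gender, obesity"). It does not say whether the GLM response is the change or the follow-up score.

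VAS, SF-36, ESR and CRP get the same scheme and the same three covariates. For these outcomes only, a further clause brings covariates into play if baseline characteristics differ significantly. Its wording is garbled: it makes the GLM itself the covariate.

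The Sample size section gives VAS inputs only: "Level of significance, a = 0.05 Two-sided test"; "b = 0.2, power of test = 80"%; "Difference between the groups, D = 16.7"; "Standard deviation, s = 27.04 (in both groups"); and "Ratio of the number of subjects in the test and placebo groups, l = 1". It gives no effect or SD for K-WOMAC.

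**The concern.** The baseline value of a symptom score is often a strong predictor of its later value. The plan adjusts for three demographic variables and leaves out this one, although it is needed anyway to compute the change.

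Subtracting baseline is not the same as adjusting for it. Subtraction fixes the slope of follow-up on baseline at 1. When the true slope is below 1, change is negatively correlated with baseline, so an arm that starts higher by chance tends to show a larger fall. Two things are at stake: a confidence interval wider than necessary, and an estimate that moves with chance baseline imbalance in a small trial.

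The article names both the tests and the covariates, so this is a stated choice and not a detail left to a fuller plan.

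**Working it through.** **Inputs from the Sample size section.** Two-sided α = 0.05, power 80%, D = 16.7 (assumed changes: "the change in the VAS score in our test and placebo groups will be −16.6 and +0.1, respectively"), SD 27.04, 1:1 allocation, 25% dropout, 37 per group. The Abstract gives 100 participants in total.

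**Assumptions, not in the article.** r between baseline and week 12 (0.3 to 0.7 shown); k, the ratio of baseline SD to week-12 SD; 27.04 as the SD of change; 37 as the evaluable number.

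**Step 1: the plan's own figure.** n = 2(1.960 + 0.842)² × 27.04² / 16.7² = 41.2, so 42 per group (43 by the noncentral t). The stated 37 is not reproduced. At 37 evaluable per group, noncentral-t power is 74.6%. Since 37/0.75 = 49.3, or 50 per group, matches the total of 100, 37 is plausibly the evaluable number, but the text does not say so.

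**Step 2: variance ratio.** With week-12 variance σ² and baseline variance k²σ²:
- Var(change) = σ²(1 + k² − 2rk)
- residual variance after ANCOVA = σ²(1 − r²)
- ratio = (1 − r²)/(1 + k² − 2rk), which becomes (1 + r)/2 when k = 1

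The ratio never exceeds 1, and equals 1 only when k = r, that is, when the slope r/k is 1.

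**Step 3: power at 37 per group** (noncentral t, D = 16.7, SD = 27.04 × √ratio; unadjusted 74.6%).

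| k | r = 0.3 | r = 0.5 | r = 0.7 |
|---|---|---|---|
| 1.0 | ratio 0.65, power 90% | 0.75, 86% | 0.85, 81% |
| 0.8 | 0.78, 84% | 0.89, 79% | 0.98, 75% |
| 0.7 | 0.85, 81% | 0.95, 77% | 1.00, 75% |
| 0.6 | 0.91, 78% | 0.99, 75% | 0.98, 75% |

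A simulation of the k = 1 case (4,000 runs, 37 per group) gave 75% against 90%, 74% against 86% and 74% against 81%. It shares the equal-variance assumption, so it confirms the formula but not the assumption. Values of k below 1 are credible for VAS, because entry requires a score above 30 mm, which truncates baseline but not follow-up.

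**Step 4: other readings of the inputs (k = 1).**
- If 37 is the number enrolled, about 28 are evaluable (37 × 0.75 = 27.75). Power is 62% unadjusted and 80%, 75% or 69% adjusted at r = 0.3, 0.5, 0.7.
- If 27.04 is the SD of a single score, power at 37 (normal approximation) goes from 61.2% to 79.5%, 75.7% to 86.6%, or 92.9% to 96.1%.

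**Step 5: chance imbalance (k = 1).** Given a baseline difference of c standard errors, the change-score z statistic has mean shift c√((1 − r)/2) and variance (1 + r)/2. Its conditional type I error is:

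| c | r = 0.3 | r = 0.5 | r = 0.7 |
|---|---|---|---|
| 0 | 1.5% | 2.4% | 3.4% |
| 1 | 4.6% | 4.8% | 5.0% |
| 1.5 | 9.2% | 8.2% | 7.0% |

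An imbalance of 1.5 SE or more, in either direction, occurs in about 13% of randomisations. At r = 0.5 it moves the estimate by 0.75 SE. With SE = 27.04 × √(2/37) = 6.29, that is 4.7 mm of VAS, against a planned 16.7.

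**The case against.** The strongest reply has four parts.

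**The size is not established.** The favourable power figures need equal variances, 27.04 as the SD of change and 37 evaluable per group, and they are VAS figures applied to a K-WOMAC analysis. This stands. A reader might infer that baseline adjustment recovers the power missing from the sample size calculation. The documents do not support that: at k between 0.6 and 0.8 the gain can be close to nothing. The mismatch over 37 per group is a separate matter and adds no weight here.

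**The planned test is valid.** This also stands. A reader might take the 7–9% conditional error to mean an inflated type I error. It does not: that error applies at a 1.5 SE imbalance, is offset by rates below 5% in well-balanced randomisations, and averages to 5%.

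**The conditional clause may bring in baseline scores.** It might, for the secondary outcomes, but it does not cover K-WOMAC. It also makes adjustment depend on a baseline significance test, which an imbalance of 1.5 SE would not normally trigger although it still moves the estimate.

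**ANCOVA gives up the Wilcoxon fallback.** This is a fair point, above all for CRP, and the fix has to provide for it.

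Two smaller limits apply. Unadjusted raw change is certain only for K-WOMAC, since the article says the secondary changes will be normalised without saying how. And the GLM response is unstated; if it is the follow-up score, leaving out baseline still costs precision, by a different factor (1 − r²).

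**Conclusion.** The point holds as one of efficiency. The K-WOMAC comparison is valid but less precise than it could be, and its estimate is sensitive to chance baseline imbalance, because a covariate already in hand is left out of a stated list. On the VAS inputs, with 27.04 taken as the SD of change and 37 evaluable per group, power goes from about 75% to 81–90% (r = 0.7–0.3, equal variances), or only to about 75–84% if the baseline SD is 0.6–0.8 of the week-12 SD. These figures illustrate the effect and do not forecast the K-WOMAC gain, for which the article gives neither SD nor correlation. Apart from one degree of freedom, adjustment does not lose precision. This is a free improvement, not an error that invalidates the plan.

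**What to change.** - **Primary analysis.** Make the between-group comparison an ANCOVA of K-WOMAC, or a repeated-measures model over weeks 6 and 12, with treatment, baseline K-WOMAC and the planned age, gender and obesity. State the response variable. Report the adjusted week-12 difference with its 95% CI.
- **Secondary outcomes.** Use the matching baseline value as a pre-specified covariate for VAS, SF-36, ESR and CRP, and delete the significance-triggered clause.
- **Non-normal outcomes.** Keep a transformation (such as log CRP) or a rank-based sensitivity analysis in place of the Wilcoxon fallback.

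The cost is a few lines of analysis text, settled before unblinding, and one degree of freedom. No new data, visits or participants are needed.

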#### Exclusion criteria

2.3.2

Subjects who have one or more of the following characteristics will not be considered for the study.

A person who has arthritis other than OA.Those who have clinically significant cardiovascular, autoimmune, infectious or neoplastic diseases in addition to joint pain.Hypertension patients not controlled by drugs with more than 160 mmHg systolic blood pressure or more than 100 mmHg diastolic blood pressure.Diabetic patients whose fasting blood glucose level is above 180 mg/dl).A person who has aspertate aminotransferase (GOT) or alanin aminotransferase (GPT) level 3 times higher than the normal upper limit.Abnormal creatinine level (more than twice the normal upper limit).Those who have taken arthritis medicines or dietary supplements for joint health within 2 weeks of visit.Subjects who have taken physical or herbal therapies (acupuncture, depression, moxibustion, etc.) for degenerative bone disease within 2 weeks of visit.Subjects who participate in other intervention trials within two months of visit 1 or plan to participate in other intervention trials after the commencement of this study.Women who are pregnant, lactating, or planning to become pregnant within 3 months.A person with mental illness or drug addiction or who is under anti-depression treatment.A person who is sensitive or allergic to food ingredients.A person who has trouble or difficulties participating in the trial as judged by the investigator.

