#### Secondary outcomes

2.8.2

Visual analog scale (VAS), which evaluates joint pain as compared with the baseline score.Korean-Short Form Health Survey 36 (KSF-36). The KSF-36 index will assess the physical and mental states of the subjects at the end of week 6 and 12.Subject's self-assessment on the change of physical and mental conditions.Investigator's evaluation based on subject's physical activity, symptoms, and emotional state.Erythrocyte sedimentation rate (ESR) and C-reactive protein (CRP) levels to measure the inflammatory markers after 12 weeks of study.

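### CRP and ESR get the questionnaire analysis with no stated scale; putting CRP on the log scale would suit its expected skew and usually gain power at almost no cost

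*Protocol article*

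**What the plan says.** Section 2.8.2 lists as a secondary outcome "Erythrocyte sedimentation rate (ESR) and C-reactive protein (CRP) levels to measure the inflammatory markers after 12 weeks of study". These are the only inflammatory markers among the efficacy outcomes, and the Introduction hypothesises an effect on inflammation as well as pain.

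Section 2.11 sets out three analyses for them, shared with VAS and SF-36:

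- **Within group:** "The total scores of VAS, SF-36, ESR, and CRP and the change of scores of each item will be analyzed by paired" t test, with no alternative named.
- **Between groups:** a two-sample t "test or Wilcoxon rank sum test will be used to evaluate whether there is a statistically significant difference". The sentence before it says that "the degree of change between the test group and the control group at each time point will be normalized".
- **Adjusted:** "In addition, the GLM will be implemented with the following variables (age, gender, obesity) as the covariate". No distribution, link or transformation is given. The marker's own baseline value is not among the three named covariates.

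For K-WOMAC, the matching phrase is that the degree of change "at each time point will be determined according to normality satisfaction", which reads as a rule for choosing between the t test and the Wilcoxon test.

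**The concern.** CRP is a concentration bounded below by zero and is usually right-skewed, and proportional changes describe it better than absolute ones. Section 2.3.2 excludes "Those who have clinically significant cardiovascular, autoimmune, infectious or neoplastic diseases in addition to joint pain" at entry, so most values should be low. That exclusion cannot prevent an infection arising before the week-12 draw, and one such value can exceed any plausible product effect many times over.

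An analysis of untransformed change gives those values, and participants with high baselines, a large share of the mean and SD. The paired t test and a normal-error GLM are exposed to this. The Wilcoxon test is not exposed in the same way. However, it does not adjust for covariates, and ranking absolute differences still uses the data less well when the effect is proportional.

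The text does not settle which scale is meant. Saying that change will be normalized could refer to a normality check, as for K-WOMAC, or to a transformation. At stake are the precision and readability of the only direct evidence on inflammation. The primary outcome is not affected.

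**Working it through.** **What can be reproduced.** The plan gives no variability, effect size or power for CRP or ESR, so there is no stated figure to check. Two inputs come from section 2.10: 37 participants per group (taken here as evaluable) and "Level of significance, a = 0.05 Two-sided test". The figure of 37 was derived for VAS. Whether it follows from its own inputs is a separate matter.

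**Assumed, because the documents are silent.** Log-normal CRP with natural-log SD 0.8 to 1.2; correlation 0.6 between baseline and week 12 on the log scale; true ratio 0.6 (a 40% reduction); and either no illness spikes or a 4% chance at each draw that the value is multiplied by ten.

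**Step 1: log-change t test without spikes, by formula.**

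- SD of log change = log-SD × √(2 × (1 − 0.6)) = 0.894 × log-SD.
- Effect = |ln 0.6| = 0.511.
- Power ≈ Φ(0.511 / (SD × √(2/37)) − 1.96), with √(2/37) = 0.2325.
- Log-SD 0.8: SD 0.716, SE 0.166, ratio 3.07, power Φ(1.11) ≈ 87%.
- Log-SD 1.2: SD 1.073, SE 0.250, ratio 2.05, power Φ(0.09) ≈ 53%.

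Simulation gives 85% and 53%, so the two agree.

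**Step 2: simulated power, same assumptions.** The rule is Wilcoxon on untransformed change if a normality check fails, otherwise the t test.

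| Spikes | Log-SD | t-or-Wilcoxon rule | Log-change t test | Difference (points) |
|---|---|---|---|---|
| None | 0.8 | 68% | 85% | 17 |
| None | 1.2 | 35% | 53% | 18 |
| 4%, tenfold | 0.8 | 54% | 63% | 9 |
| 4%, tenfold | 1.2 | 31% | 42% | 11 |

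With spikes, a normal-error GLM on untransformed change has only 9% to 13% power.

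**Step 3: a second set of assumptions.** Log-SD 0.7 or 1.0, correlation 0.6, true ratio 0.7 or 0.5, median baseline 1.5, 37 per arm, 2,000 runs per scenario. Illness, where present, adds 15 to 60 units to 4% of values. The last column is a log-scale ANCOVA on log baseline.

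| Ratio | Log-SD | Spikes | Rule | Wilcoxon, log change | t test, log change | Log ANCOVA |
|---|---|---|---|---|---|---|
| 0.7 | 0.7 | none | 54% | 66% | 67% | 76% |
| 0.7 | 1.0 | none | 31% | 41% | 41% | 47% |
| 0.5 | 0.7 | none | 96% | 100% | 100% | 100% |
| 0.5 | 1.0 | none | 71% | 89% | 91% | 96% |
| 0.7 | 0.7 | 4% | 42% | 51% | 28% | 39% |
| 0.7 | 1.0 | 4% | 23% | 29% | 22% | 28% |
| 0.5 | 0.7 | 4% | 84% | 96% | 71% | 82% |
| 0.5 | 1.0 | 4% | 57% | 78% | 59% | 72% |

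Three things follow:

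1. Without spikes, every log-scale method beats the rule.
2. With very large additive spikes, the log-change t test falls below the rule in three of four scenarios and log ANCOVA falls slightly below it in two. The gain from a log-scale mean comparison is therefore usual but not universal.
3. With a rank test throughout, ranking log change beats the rule in all eight scenarios.

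In the four spike scenarios, the normal-error GLM on untransformed change has 5% to 8% power. The normality check (Shapiro-Wilk at 0.05) failed in 89% to 100% of runs, so the rule chose Wilcoxon almost every time.

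**Step 4: type I error.** With no true effect, every method stayed at about 4% to 6%. The issue is efficiency and interpretability, not false positives.

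The within-group paired t test was not simulated, and no calculation was made for ESR.

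**The case against.** The strongest defence is the sentence on the Wilcoxon test. It covers the unadjusted comparison of the randomised groups, whereas the paired t test is within-group and the GLM is an addition. A reader might infer that a few intercurrent illnesses would decide the CRP result. The documents do not support that: a rank test limits the weight of extreme values, and the plan names one for these markers. This part of the defence stands.

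A reader might also infer that a real anti-inflammatory effect is likely to be missed. That does not follow either. The variability, illness rate and effect are all assumed, and across the second set of assumptions the rule ranges from 23% to 96% power. The log-change t test itself reaches only 42% to 63% under tenfold spikes, so much of the shortfall reflects group size and assumed variability, not scale.

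The text never says that changes are untransformed, and section 2.11 expands GLM as a generalized linear model, which could allow a non-normal distribution. The plan is therefore unclear on scale, not demonstrably wrong. The rule for choosing the test is stated legibly only for K-WOMAC, so applying it to CRP is a charitable reading.

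Finally, detection-limit handling and sensitivity analyses for draws during infection are details that an article may leave to the full protocol or SAP. Their absence is no finding. Applying the words score and item to blood markers is an editorial slip.

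What remains is that the paired t test has no alternative, the adjusted model has no stated scale, and the wording on normalization needs to be made clear.

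**Conclusion.** The point holds as a cheap improvement to a secondary analysis. The protocol article carries the questionnaire analysis over to CRP and ESR and leaves their scale unclear. The unadjusted between-group test is reasonably protected by the Wilcoxon option. The paired t test is sensitive to the skew expected of CRP, and so is the GLM if run with normal errors on untransformed change.

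Under the first set of assumptions, a log-change t test gains roughly 9 to 18 percentage points of power over the t-or-Wilcoxon rule. Under very large additive spikes that gain can disappear or reverse, which is why a rank test should be kept alongside. All sizes rest on assumed CRP behaviour and on 37 evaluable participants per arm. For ESR the point is conditional on its being skewed.

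**What to change.** Replace the shared sentence for the two markers with a short paragraph of their own:

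- State that CRP is log-transformed for the paired test, the between-group test and the GLM. Treat ESR the same way if it is skewed, deciding this on blinded pooled data.
- Specify the GLM as a normal-error model on the log scale, with log baseline added to age, gender and obesity.
- Report the geometric mean ratio of HT083 to placebo with its 95% CI.
- Keep the Wilcoxon rank sum test as a sensitivity analysis, preferably on log change.
- Replace the statement that change will be normalized with one that names the scale and the test. The score and item wording can be dropped for these markers in the same edit.

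The cost is a change of wording and a transformation of data already being collected, with no extra visits or samples. It should be settled before unblinding. The one downside is that results are read as ratios, not as mg/L or mm/h; group medians on the original scale can be tabulated alongside.

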### Randomization and blinding

2.5

A randomization list will be created by an independent analyst using block randomization method in SAS version 9.2 (USA). Participants will be given a randomized code and will receive the treatment product labeled with the same code. Participants will be randomly allocated to either the test or the placebo group in a 1:1 ratio. The placebo will be used to compare the efficacy of the test product. All participants and the research personnel will remain blinded to the assigned treatment until the end of the trial. The appearance of the test food and the placebo product will be identical. Unblinding will be permissible under emergency circumstances which are defined in the study protocol.

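### Section 2.11 lets the data choose the analysis: a normality check picks the K-WOMAC test and, on the likely reading, baseline p values pick secondary-outcome covariates; the cost is mainly precision and clarity, not type I error

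*Protocol article*

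**What the plan says.** All the analysis rules are in section 2.11 (Statistical analysis) of the protocol article.

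- **Primary outcome, K-WOMAC.** Paired t tests are run on the scores. Between groups, "the degree of change between test and the control group at each time point will be determined according to normality satisfaction", by a t test or a Wilcoxon rank sum test. A GLM with age, gender and obesity follows in addition. Section 2.8.1 lists both week 6 and week 12 for this outcome.
- **Secondary outcomes, VAS, SF-36, ESR and CRP.** The same pair of between-group tests is offered, followed by a GLM with the same three covariates and then this condition: "if there is a statistically significant difference among the baseline characteristics, the GLM will be considered as the covariate".

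The sample size in section 2.10 is built on a difference in mean VAS change: "Difference between the groups, D = 16.7", with a standard deviation of 27.04 in both groups. Allocation is random (section 2.5): "Participants will be randomly allocated to either the test or the placebo group in a 1:1 ratio".

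**The concern.** Two rules make the analysis depend on the data it is meant to judge.

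**Normality rule (K-WOMAC).** A t test compares means and a Wilcoxon test compares ranks. Because the choice is made separately at each time point, the same outcome could be judged on means at one visit and on ranks at the other. The sample size is planned on a difference in means, so a switch to ranks also leaves the planning basis. The GLM then adds a further treatment p value, and nothing in the section ranks it against the selected test.

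**Baseline-significance rule (VAS, SF-36, ESR and CRP).** With random allocation, baseline differences arise by chance. A significance test of them carries no information on whether a variable predicts outcome. It can bring in an irrelevant variable and leave out a strong predictor whose imbalance falls short of p < 0.05.

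**Missing baseline score.** The baseline score is likely the strongest predictor of change, yet it is not among the named covariates. For the secondary outcomes it could enter only by being significantly imbalanced. For K-WOMAC no route is stated.

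At stake are a clearly defined primary result and precision that already collected data would supply.

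**Working it through.** **1. The plan's own figure.** Inputs from section 2.10: "Level of significance, a = 0.05 Two-sided test", power 80%, difference 16.7, SD 27.04.

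n per group = 2 × [(1.960 + 0.842) × 27.04 / 16.7]² = 41.15, so 42.

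The plan states: "We assume that with a dropout rate of 25%, 37 participants will be included in each group". The figure of 37 is not reproduced, which is a separate matter. Read as evaluable patients, 37 / 0.75 = 49.3, so 50 per group, which matches the total of 100 in the Abstract. I therefore use 37 per group as the number analysed.

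Unadjusted power at 37 per group = Φ(16.7/27.04 × √(37/2) − 1.960) = Φ(0.696) = 75.7%, or 74.6% with the t distribution.

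**2. Type I error of the written rules.** Null simulation with 37 per group and 5,000 trials per error distribution (Monte Carlo error about 0.3 points). Assumptions: Shapiro-Wilk at 0.05 in each arm; 10 independent baseline variables, of which 3 are always adjusted for and 7 are tested; change correlated with baseline.

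| Rule | Normal | Exponential | t with 3 df |
|---|---|---|---|
| Normality-selected test | 4.7% | 5.7% | 5.3% |
| GLM, fixed covariates | 4.8% | 5.3% | 4.8% |
| GLM, covariates added by baseline p value | 4.1% | 4.4% | 3.8% |
| Success on the selected test or the added-covariate GLM | 5.9% | 7.3% | 6.6% |

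The last row fits the secondary outcomes. For K-WOMAC, whose GLM covariates are fixed, a separate run of 8,000 null trials with normal data gave 5.0% for the selected test alone and 5.8% for success on either result.

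**3. How often chance would change the covariate set.** The article does not say how many baseline characteristics will be tested, so assume 5–10 independent ones. If they include age, gender and obesity, which are always in the GLM, 2–7 remain that could be added: 1 − 0.95² = 10% to 1 − 0.95⁷ = 30%. If those three are not among them: 1 − 0.95⁵ = 23% to 1 − 0.95¹⁰ = 40%. This is how often the model would change. It is not a false-positive rate.

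**4. Precision lost by omitting the baseline score.** Take 27.04 as the SD of change and assume equal variance at baseline and follow-up, with correlation ρ. The variance of change is 2σ²(1 − ρ) and the ANCOVA residual variance is σ²(1 − ρ²), so their ratio is (1 + ρ)/2.

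- ρ = 0.5: ratio 0.75, SD = 27.04 × √0.75 = 23.42, power = Φ(16.7/23.42 × 4.301 − 1.960) = Φ(1.107) = 86.6%.
- ρ = 0.3: ratio 0.65, SD = 21.80, power = Φ(1.335) = 90.9%.

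Allowing for four covariates (baseline, age, gender, obesity) with a noncentral t on 74 − 6 = 68 df and a variance factor of 1 + 4/67 gives 83.6% and 88.4%. Simulation of 6,000 trials at each correlation gave 84.7% and 88.3%, against 74–75% for the normality-selected test. The gain shrinks as ρ rises: at ρ = 0.7 the SD is 24.93 and power with four covariates is 78.8%.

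**The case against.** The best defence is that neither rule does much numerical harm. Step 2 supports this: each stays close to or below 5%. A reader might infer that the normality check itself inflates false positives; the figures do not support that.

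A reader might also infer that baseline p values choose the covariates for the primary outcome. They do not. The rule appears only with VAS, SF-36, ESR and CRP, and the K-WOMAC GLM has fixed covariates. Even for the secondary outcomes the sentence is garbled, since a model cannot be a covariate. Adding covariates on significance is the most plausible repair, but it remains a reading.

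A third tempting inference is that the sponsor may report the best of t, Wilcoxon and GLM, which would give 6.4% on normal data in the 8,000-trial run. The plan does not allow this, because the normality check picks one of the first two. Even the figure of about 6% requires success on either remaining result to count, which the article does not say. The GLM can be read as supplementary.

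Finally, the ranking of the analyses could sit in a full protocol or SAP that is not shown. That is fair for the silence about which result decides. It does not cover the two rules, which the article states and a later document would have to contradict in order to remove.

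**Conclusion.** The point holds as a badly chosen method that should be corrected. It is not a threat to the trial's validity. The normality-based choice for K-WOMAC is plain in the text; the baseline-significance rule, for the secondary outcomes only, rests on the most plausible reading of a defective sentence.

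Type I error stays near 5% under either rule alone. If success on either of two unranked results counted, it would be about 6% with normal data, and up to 7.3% in the secondary-outcome form with skewed data.

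The larger cost is a result that is not defined in advance, and lost precision: power of about 75% against about 84–88% with baseline adjustment. That comparison assumes 37 analysed per group, 27.04 as the SD of change, equal variances and a correlation of 0.5–0.3. It uses the plan's VAS figures, because the article gives none for K-WOMAC, so it illustrates the primary outcome and does not estimate its power.

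**What to change.** Rewrite section 2.11 as follows:

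- Name one between-group analysis for every outcome: ANCOVA with treatment, baseline score, age, gender and obesity, whatever the normality or baseline p values.
- Name one visit as primary for K-WOMAC. Without this, a fixed model still leaves two unranked results.
- Delete the normality rule and the baseline-significance rule.
- Keep the t test or Wilcoxon test as a labelled sensitivity analysis.

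A log scale for CRP and ESR would be an optional extra that this point does not require.

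The cost is a short rewrite, made before unblinding, with no extra patients or visits: the covariates are already named, and the planned comparisons with baseline already need the baseline scores. The trade-off is reliance on a linear model, which the rank-based sensitivity analysis covers.

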**Methods::**

This is a randomized, double-blind, and placebo-controlled study. A total of 100 eligible participants will be divided into two groups and will be given HT083 and a placebo for 12 weeks in 1:1 ratio. Treatment results will be assessed using a visual analog scale (VAS), Korean-Short Form health survey-36 score (SF-36), personal evaluation, and laboratory analysis.

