**Discussion::**

This trial is expected to provide clinical evidence on the effectiveness and the safety of HT083 as a natural treatment for mild OA.

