This study has few limitations. First, this trial will be conducted on only one ethnic group. Therefore, it is unknown whether our data will be representative of other parts of the world other than Korea. Second, the small size of the test group makes it hard to generalize the data. However, given the analgesic and anti-inflammatory properties of *P. lactiflora* and *C. myrrha* as well the in vivo anti-osteoarthritic effects of HT083, we hope that this trial will demonstrate the efficacy and safety of HT083 in patients with mild OA.

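### The article's only between-group safety inference is a test of no difference, and at 37 to 50 per arm a non-significant result cannot support the hoped-for demonstration of safety

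*Protocol article*

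**What the plan says.** Section 2.11 (Statistical analysis) codes treatment-emergent events in MedDRA, tabulates all adverse events with their incidence, and then gives the one between-group safety comparison in the article: "The proportion of human subjects with adverse reactions between groups will be calculated and analyzed using Chi-square test or Fisher exact test". Section 2.8.3 also lists vital signs, clinical tests and an echocardiogram as safety outcomes.

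On what the trial is to show, the Abstract's Discussion paragraph says it is "expected to provide clinical evidence on the effectiveness and the safety of HT083". Section 3 closes with "we hope that this trial will demonstrate the efficacy and safety of HT083 in patients with mild OA".

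On size, the Abstract says "A total of 100 eligible participants will be divided into two groups", section 2.5 fixes 1:1 allocation, and section 2.10 says "We assume that with a dropout rate of 25%, 37 participants will be included in each group". That calculation uses the VAS pain score only. No adverse-reaction rate, safety margin or power for safety is stated. Section 3 mentions the small size, but only as a limit on generalizing.

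**The concern.** A chi-square or Fisher test asks whether the data contradict equal rates. It does not ask whether a relevant excess has been ruled out. In a trial sized for a pain score, the test can easily be non-significant while the true rate on HT083 is well above placebo.

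The likely summary of such a result is that adverse reactions did not differ significantly. Set beside a stated hope of demonstrating safety, that sentence invites the reading that safety has been shown. An interval for the difference in proportions would show which excess risks remain open, and a p-value does not.

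**Working it through.** **Inputs from the article**
- 100 participants at 1:1 (Abstract, section 2.5), so 50 per arm.
- 37 per group and 25% dropout (section 2.10).
- Two-sided 0.05. Section 2.10 states this for efficacy, and it is assumed here for the safety test.

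**The plan's own figure.** There is none for safety. The two sizes fit together if 37 is the number left after dropout: 37 / (1 - 0.25) = 49.3, so 50 per arm and 100 in total. I therefore use 37 and 50. (The efficacy inputs give 2 × (1.960 + 0.842)² × 27.04² / 16.7² = 41.15, so 42 per group and not 37. That is a separate matter and does not affect this point.)

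**Assumed.** All adverse-reaction rates, because the article gives none.

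**Power.** With p0 the rate on placebo, p1 the rate on HT083, and n per arm, sum over all pairs of counts (a on HT083, b on placebo):

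power = Σ Bin(a; n, p1) × Bin(b; n, p0) × [test rejects at 0.05 for (a, b)]

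This is exact enumeration for the two-sided Fisher test and for the uncorrected Pearson chi-square test, the two tests that section 2.11 names.

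| Placebo vs HT083 | 50 per arm: Fisher / chi-square | 37 per arm: Fisher / chi-square |
|---|---|---|
| 5% vs 10% | 6.3% / 14.5% | 3.5% / 13.5% |
| 10% vs 20% | 19.5% / 30.3% | 14.2% / 23.0% |
| 15% vs 30% | 35.4% / 44.3% | 25.3% / 33.8% |
| 5% vs 15% | 24.4% / 39.3% | 15.5% / 32.5% |
| 10% vs 30% | 64.0% / 73.4% | 48.8% / 59.3% |
| 15% vs 45% | 88.7% / 92.2% | 75.9% / 82.8% |

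For a tripling, power passes 50% once the placebo rate exceeds about 8.1% (Fisher) or 6.3% (chi-square) at 50 per arm, and about 10.2% or 8.3% at 37 per arm.

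**What an interval would show.** Newcombe's method combines the Wilson limits (l, u) of each arm, with 1 = HT083 and 2 = placebo:
- lower limit = d - √[(p1 - l1)² + (u2 - p2)²]
- upper limit = d + √[(u1 - p1)² + (p2 - l2)²]

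For 5/50 in each arm, d = 0. The Wilson limits are 0.0435 and 0.2136. The half-width is √[(0.1 - 0.0435)² + (0.2136 - 0.1)²] = √(0.0032 + 0.0129) = 0.127. The 95% interval is -12.7 to +12.7 points, with Fisher p = 1.0.

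For 6/50 on HT083 and 2/50 on placebo, an observed tripling, Fisher p = 0.27. The difference is +8 points, with a 95% interval of -3.4 to +20.2.

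**The case against.** The strongest reply has four parts.

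1. **No decision rule.** Nowhere does the article say that a non-significant p-value will be taken as proof of safety. The phrases about safety express hope and expectation. This stands: the harm is a risk of misreading, not a stated rule.

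2. **The test is not the whole safety assessment.** Incidence is tabulated, both proportions are calculated, and further safety outcomes are collected. This stands too, and a reader could derive an interval from the counts. But tabulation alone does not say how large an excess remains possible, and the test is the only between-group inference described.

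3. **Intervals may be left to the full protocol or SAP.** Their absence from a condensed article would indeed be no finding. The point is different: the article positively names a test of no difference as the inference and pairs it with a safety aim that such a test cannot serve.

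4. **Low power depends on the event rate and the test.** A reader might infer that the design misses even a tripling of events most of the time. The documents do not support that. They give no event rate, and the planned analysis counts subjects with adverse reactions, not one rare event type. At 10% against 30% with 50 per arm, the tripling is found with 64% (Fisher) or 73% (chi-square) power. At 15% against 45% it is found about nine times in ten. Quoting Fisher alone would also understate the power, since chi-square is the other named option.

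**Conclusion.** The point holds in a bounded form. The between-group inference named in section 2.11 does not match the safety claim that the Abstract and section 3 look for. That mismatch does not depend on the event rate, because non-significance is not evidence that rates are similar.

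How often a real excess would go unnoticed does depend on assumed rates. At 37 to 50 per arm and two-sided 0.05, under either named test, a doubling from 10% or less would be missed at least about 70% of the time. A tripling from 5% would be missed about 61% to 76% of the time at 50 per arm and 67% to 84% at 37. A tripling from 10% would usually be found at 50 per arm and is close to even at 37 (49% Fisher, 59% chi-square).

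The primary analysis and the conduct of the trial are untouched.

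**What to change.** In section 2.11, make the risk difference (HT083 minus placebo) in the proportion of subjects with adverse reactions, with a 95% confidence interval such as Newcombe's, the basis of the between-group safety comparison. Keep the tabulated incidence, and treat any chi-square or Fisher p-value as descriptive.

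In the Abstract's Discussion paragraph and in section 3, word the safety conclusion as a description of tolerability over 12 weeks, not as a demonstration of safety. The trial report should follow the same wording.

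This changes analysis and report wording only and needs no extra data or participants. The cost is a more modest safety claim.
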